### Secondary outcome measures

Secondary outcomes will be assessed during pregnancy and until children reach the age of 48 months, specifically: blood lipid profile, lung function (peak expiratory flow - nSpire Health PiKo-1® - nSpire Health, Inc. - [name]), gestational diabetes (self-reported, by the time of delivery), gestational weight gain (calculated based on pre-gestational weight and weight at admission to deliver), mode of delivery (vaginal or cesarean section), birth weight (in grams), length at birth (in cm) and fetal growth (according to the new Intergrowth-21st fetal growth curves [26]). At three months post-partum two outcomes will be measured: post-partum weight retention (difference between current weight and pre-gestational weight) and depression (measured by the Edinburgh Postnatal Depression Scale). Infant neurodevelopment will be assessed (measured by the Battelle Developmental Inventory) at the 12, 24 and 48-month visits [27].

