## Aim

The aim of this study is to present the experimental protocol of a trial aimed at evaluating the effectiveness of an exercise intervention, by comparing the intervention and control groups with infant outcomes assessed later in life. Data will be collected on: prematurity, gestational age, gestational weight gain, blood pressure, fasting blood glucose, postpartum weight retention, postpartum depression and birth weight.

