### Exclusion criteria

During the first contact, women will be interviewed about several aspects of their overall health, and those presenting any of the conditions described in the Table 1 will not be eligible for the trial.

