### Logistics and setting

The study begins with one initial contact with the mother, prior to the 16th week of gestation, when interviewers ask for contact information, conduct a brief interview and hand a leaflet explaining the controlled trial. After enrollment in the study, women will be invited to go to the Epidemiology Research Center to collect baseline data, that is, blood and urine sampling, anthropometry, blood pressure and lung function. The same assessments (in both groups) will be repeated at eight and 16 weeks

after baseline. The facilities of the Federal University of Pelotas at the Physical Education School will be used for the intervention. A second interview at hospital will take place soon after birth (when children will be measured and mothers will be asked about many aspects of their pregnancy). After these initial data collections, when children are three, 12, 24 and 48 months, interviews will be carried out at the Epidemiologic Research Center or the participant's household. Fig. 2 shows the recruitment flowchart and subsequent data collections.

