### Intervention procedures: exercise protocol

The intervention will start between the 16th and 20th week of gestation and will last 16 weeks. Workouts will be guided and supervised by a team of five previously trained physical education professionals. A set of exercises will be suggested for each workout, involving aerobic activities (treadmill or stationary bike), strength training (dumbbells, machines or elastic bands) and floor exercises. The intensity of the exercises will be set according to each woman's perceived effort (within the range of 12 to 14 on the Borg Scale) [25], and will be altered according to the progress of pregnancy. The workload will change according to the week of the intervention, and the stages are described in Table 2.

Each session will last around 60 min, and will include aerobic exercises (treadmill or stationary cycling), strength training (with focus on major muscle groups and pregnancy-specific exercises to help alleviate low back pain, and work abdominal and pelvic floor muscles to prevent urinary incontinence) and will end with stretching exercises. The exercises are described in the Table 3.

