### Primary outcome measures

Preterm birth (gestational age below 37 weeks of pregnancy), and pre-eclampsia (blood pressures above 140/90 mmHg and proteinuria above 15.0 mg/dL) will be assessed during pregnancy and soon after birth.

[figure not shown]

**Fig. 1** Study design

**Table 1** Exclusion criteria of the randomized controlled trial

| Exclusion criteria            | Description                                                   |
|-------------------------------|---------------------------------------------------------------|
| Age                           | Below 18 years                                                |
| Hypertension                  | Diagnosed before pregnancy/Self-reported                      |
| Diabetes                      | Diagnosed before pregnancy/Self-reported                      |
| Preterm birth                 | History of previous preterm birth                             |
| Miscarriage                   | History of previous miscarriage                               |
| Heart disease                 | Diagnosed before pregnancy/Self-reported                      |
| In vitro fertilization | Fertilization in the current pregnancy                        |
| Double/twin pregnancy         | Twin pregnancies confirmed by ultrasound                      |
| Persistent bleeding           | Women presenting persistent bleeding                          |
| Severe obesity                | Body mass index above 35 kg/m                     |
| Heavy smokers                 | Smoking more than 20 cigarettes a day                         |
| Active women                  | Weekly leisure-time physical activity > 150 min/Self-reported |

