### Statistical analysis

Statistical analyses will be conducted on an intention-to-treat basis, but secondary analyses will be performed, including only those considered adherent to the protocol. Baseline characteristics will be presented using descriptive statistics to compare both groups.

According to the type and distribution of variables, between-groups differences will be evaluated using adequate tests. Continuous variables will be analyzed by t tests (for symmetrically distributed data), or Mann-Whitney U tests (for asymmetrical data). Categorical

[figure not shown]

**Table 2** Stages of training routines during pregnancy according to week of intervention

| Weeks of intervention | Warm-up | Aerobic exercise | Strength training/Floor exercises | Stretching |
|-----------------------|---------|------------------|-----------------------------------|------------|
| 1 to 4, Stage 1       | 5 min   | 15 min           | 35 min (sets: 3 × 12 repetitions) | 5 min      |
| 5 to 10, Stage 2      | 5 min   | 20 min           | 30 min (sets: 3 × 10 repetitions) | 5 min      |
| 11 to end, Stage 3    | 5 min   | 25 min           | 25 min (sets: 3 × 8 repetitions)  | 5 min      |

variables will be analyzed with chi-square tests or Fisher's exact test, as appropriate. General linear model or logistic regression will be employed to control for confounding factors. More specifically, based on the perinatal study information, preterm birth, gestational diabetes and eclampsia incidences will be compared in the two groups using chi-square tests, followed by multivariable analyses when adequate; linear regressions will be carried out to evaluate potential differences in birth weight, gestational weight gain and lipid profile. Analysis will be carried out in the statistical package STATA 12.0 (StataCorp, [name]) and significance will be set at 5 %.

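### The gestational diabetes outcome has no start to its onset window, so diagnoses made in this pregnancy before randomisation would count (minor, secondary outcome)

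*Protocol*

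**What the plan says.** Under Secondary outcome measures the outcome is "gestational diabetes (self-reported, by the time of delivery". The phrase fixes how the outcome is obtained and when the window closes, but not when it opens.

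The diabetes row of Table 1 reads "Diagnosed before pregnancy/Self-reported". The Exclusion criteria section applies the table at the first contact: "those presenting any of the conditions described in the Table 1 will not be eligible for the trial". Logistics and setting places that contact "prior to the 16th week of gestation". On the intervention, the exercise protocol says: "The intervention will start between the 16th and 20th week of gestation and will last 16 weeks".

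Under Statistical analysis, "preterm birth, gestational diabetes and eclampsia incidences will be compared in the two groups using chi-square tests", and "Statistical analyses will be conducted on an intention-to-treat basis". No at-risk set or onset window is given for gestational diabetes. The Aim lists "fasting blood glucose" among the data to be collected, and blood is drawn at baseline, but neither is linked to eligibility or to this outcome.

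**The concern.** A woman told in early pregnancy that she has gestational diabetes passes the diabetes exclusion, because her diagnosis did not precede the pregnancy. At delivery she truthfully answers yes and is counted. Her event came before allocation, so exercise could not have prevented it. The analysis section calls the compared quantity an incidence, but the definition also admits cases already present at entry.

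The issue is the time of onset, not the accuracy of self-report. At stake is the interpretation of the risk ratio. The Background says that trials so far have not shown clearly whether exercise affects diabetes in pregnancy. A ratio diluted by cases present at entry would be harder to set beside that evidence.

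**Working it through.** **Can an early case enter and be counted?**
- Eligibility: Table 1 bars only diabetes diagnosed before pregnancy.
- Timing: first contact is before week 16 and exercise begins at weeks 16 to 20, so diagnoses can arise before first contact, or between it and randomisation.
- Counting: any self-report up to delivery scores as an event.
- Removal: no section takes such cases out.

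One might read the Table 1 entry as also barring any diabetes reported at first contact. The row for active women pairs a threshold with the same self-report label, so the label names the method of ascertainment. Even on the wider reading, diagnoses between first contact and randomisation would still count.

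**Inputs.** From the Protocol: 213 intervention and 426 control women, 5 % significance (taken as two-sided, since sidedness is not stated) and a 30 % risk reduction, i.e. a risk ratio of 0.70. The sample size section does not name gestational diabetes, so applying 0.70 to it is an assumption. The Protocol gives neither a gestational diabetes rate nor the share diagnosed early. Assumed: total control rate *c* = 3 %, 5 %, 10 %; share of control cases preceding randomisation *f* = 10 %, 25 %, 50 %. There is no stated figure for this outcome to reproduce.

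**Formulas.**
- Prevalence at entry, equal in both arms in expectation: *a* = *cf*.
- Control risk after entry among women still at risk: *i* = (*c* − *a*)/(1 − *a*).
- Intervention risk with early cases counted: *a* + (1 − *a*) × 0.70*i*.
- Observed risk ratio: *f* + 0.70(1 − *f*).
- Risk difference in all randomised women = (1 − *a*) × risk difference in women still at risk.

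**Example, *c* = 5 %, *f* = 25 %.** *a* = 0.0125; *i* = 0.0375/0.9875 = 0.0380. Intervention risk = 0.0125 + 0.02625 = 0.03875. Observed ratio = 0.03875/0.05 = 0.775. Risk difference: 0.01125 in all randomised women against 0.01139 in women at risk, a factor of 0.9875.

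**Ratio.**
- *f* = 10 %: 0.10 + 0.70 × 0.90 = 0.73
- *f* = 25 %: 0.25 + 0.70 × 0.75 = 0.775
- *f* = 50 %: 0.50 + 0.70 × 0.50 = 0.85

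**Risk difference.** The factor 1 − *a* runs from 0.997 (*c* = 3 %, *f* = 10 %) to 0.95 (*c* = 10 %, *f* = 50 %).

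**Power.** Normal approximation for two proportions: Φ[(|difference| − 1.96 × pooled SE)/unpooled SE]. It uses 213 and 426 women with early cases counted, and 213(1 − *a*) and 426(1 − *a*) with them left out.

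| Control rate | No early cases | *f* = 10 %: counted / left out | *f* = 25 %: counted / left out | *f* = 50 %: counted / left out |
|---|---|---|---|---|
| 3 % | 8.4 % | 7.5 / 7.9 % | 6.3 / 7.1 % | 4.6 / 5.6 % |
| 5 % | 12.3 % | 10.6 / 11.3 % | 8.4 / 9.9 % | 5.7 / 7.5 % |
| 10 % | 22.6 % | 18.9 / 20.5 % | 14.1 / 17.3 % | 8.3 / 12.3 % |

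Counting early cases costs about 0.4 to 4 percentage points. The approximation uses only the tail in the direction of benefit, which is why one entry falls below 5 %.

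**The case against.** The strongest reply is that the definition does not say early diagnoses count. It is silent, and the word incidences in the analysis section may signal that only new cases are meant. An at-risk set for a secondary outcome is also often left to the statistical analysis plan. The reply has some force: the intent may well be right. But the Protocol does fix a counting rule, and applied as written that rule includes early cases.

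The reply on size stands. The documents give no evidence of how many diagnoses precede weeks 16 to 20; if few do, the effect is small. The planned test compares proportions, and the risk difference hardly moves. The outcome does not drive the sample size and has little power either way.

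Four stronger readings are tempting, and the documents do not support them:
- That the comparison is biased toward a false positive. Randomisation balances early cases in expected proportion, so the test keeps its level. A chance imbalance is already covered by the 5 % error rate.
- That material dilution is established. It rests on the assumed share *f*.
- That gestational diabetes is the only glycaemic measure in the plan. It is the only one listed under Secondary outcome measures or named under Statistical analysis, but the Aim also lists "fasting blood glucose".
- That a diagnosis date asked at delivery would settle the matter cleanly. Women know their allocation by then, so recall could differ by arm, and excluding on recalled dates could bring in a bias that the present definition avoids.

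**Conclusion.** The point holds as a minor, inexpensive correction to one secondary outcome. The definition lacks a start to the onset window, and no section closes the gap. If 10 % to 50 % of control cases precede randomisation and the true ratio is 0.70, the observed ratio would be 0.73 to 0.85. The risk difference keeps 95 % to 99.7 % of its size, and power falls by at most about 4 points from a base of about 8 % to 23 %. These figures assume control rates of 3 % to 10 %, equal expected prevalence at entry in both arms, and a two-sided 5 % test. The distortion is toward no effect. It does not touch the primary outcomes or the validity of the trial.

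**What to change.** Under Secondary outcome measures, define the outcome as gestational diabetes first diagnosed after randomisation. At the baseline visit, before allocation, ask about and record any diabetes diagnosis in the current pregnancy. Leave women with such a diagnosis out of this outcome's at-risk set in both arms alike, and keep them in all other analyses. Because the exclusion rests on information recorded before allocation, the comparison stays randomised.

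If baseline fasting glucose is also to define the at-risk set, state that the sample is drawn before allocation, which the Protocol does not say at present, and have the sponsor pre-specify the cut-off. Use a diagnosis date recalled at delivery only in a sensitivity analysis. Report the comparison of all randomised women as well.

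The cost is one baseline question, one sentence of definition and a slightly smaller denominator for this outcome: at most 5 % fewer women in the scenarios above.

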## Abstract

**Background:** Preterm birth is associated with most cases of neonatal deaths and negative health outcomes, and hypertensive disorders. Hypertension is influenced by maternal behavior, such as physical activity. Physical activity is associated with better outcomes for mother and fetus, besides healthier weight gains during pregnancy. Few women are physically active during pregnancy and few clinical trials have been carried out with pregnant women. The aim of this paper is to describe the protocol of a controlled trial evaluating whether regular exercise during pregnancy may result in improved maternal-child health and neonatal outcomes.

**Methods/Design:** The PAMELA (Physical Activity for Mothers Enrolled in Longitudinal Analysis) trial is a randomized controlled trial nested in a birth cohort study. Eligible women belonging to the birth cohort will be invited (between the 16th and 20th week of gestation) to enroll in the trial. Baseline data (blood and urine samples, anthropometry and pulmonary function) will be collected at enrollment. The same assessments will be repeated eight and 16 weeks after baseline. After randomization, women will be allocated into either one of these groups: control, 426 women who will be advised to keep their usual daily activities; and intervention, 213 women who will engage in an exercise program, three sessions a week. At least 70 % attendance over 16 weeks will be required to be considered compliant to the intervention. Exercise protocol will include aerobics, strength and flexibility training. Maternal and child outcomes will be measured at the 36th week of gestation, at birth and at three, 12, 24 and 48 months postpartum. An intention-to-treat analysis will be performed.

**Discussion:** Few women are active during pregnancy and a vast majority decrease their activities or even quit exercising. We present a population-based regular exercise intervention focused on the prevention of hypertension, pre-eclampsia and preterm birth. Data on the underlying cohort will allow future analysis using different outcomes with low probability of recall bias or misclassification of exposure status. Results will potentially influence prenatal care counseling in regards to physical activity.

**Trial registration:** Clinicaltrials.gov identifier: NCT02148965, registered on 22 May 2014.

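### Gestational weight gain includes all gain before randomisation; adjusting for baseline-visit weight would remove that noise and leave the outcome definition unchanged

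*Protocol*

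**What the plan says.** The Protocol, Secondary outcome measures, lists "gestational weight gain (calculated based on pre-gestational weight and weight at admission to deliver" among the secondary outcomes. The same section takes post-partum weight retention as weight at three months less pre-gestational weight. It does not say how pre-gestational weight is obtained.

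On timing, the Abstract says that women "will be invited (between the 16th and 20th week of gestation) to enroll in the trial". Intervention procedures: exercise protocol adds: "The intervention will start between the 16th and 20th week of gestation and will last 16 weeks".

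On what is measured, the Abstract states: "Baseline data (blood and urine samples, anthropometry and pulmonary function) will be collected at enrollment". Logistics and setting continues: "The same assessments (in both groups) will be repeated at eight and 16 weeks" after baseline. Weight is not named, but it is the ordinary content of anthropometry.

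On analysis, the Statistical analysis section says that "linear regressions will be carried out to evaluate potential differences in birth weight, gestational weight gain and lipid profile". It names no covariate for this comparison. Regression adjustment is mentioned only as a way to deal with confounding.

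**The concern.** The tested outcome is the sum of two parts: gain up to the baseline visit, which allocation cannot influence, and gain after it, which it can. Any effect of exercise sits wholly in the second part. The first part adds variation between women and carries no information about treatment. It also brings in whatever error there is in a pre-gestational weight that the trial cannot have measured itself, because women are recruited when already pregnant.

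What is at stake is the precision of a declared secondary comparison, and of post-partum weight retention, which starts from the same pre-gestational weight. The trial apparently collects the measurement that would remove this variation, yet neither the outcome definition nor the stated analysis uses it.

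**Working it through.** The Protocol gives no effect size, standard deviation or power for weight gain, so there is no stated figure to reproduce.

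**1. Share of the interval before randomisation.** Inputs: start at 16 to 20 weeks (Protocol); delivery at 40, 37 or 34 weeks (chosen for illustration).

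- 40 weeks: 16/40 = 40% to 20/40 = 50%
- 37 weeks: 16/37 = 43% to 20/37 = 54%
- 34 weeks: 16/34 = 47% to 20/34 = 59%

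These are shares of time, not of kilograms or of variance.

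**2. Why covariates remove the early part.** Let P be recorded pre-gestational weight, B weight at the baseline visit and D weight at admission for delivery. Total gain is T = D − P = (B − P) + (D − B). Regress T on arm, P and B. Because T differs from D, and from D − B, only by a linear combination of P and B, the arm coefficient and its standard error are identical whichever of the three is the response. The early gain drops out although the outcome is still total gain. Error in P drops out of the response too, since the same recorded P is a covariate. The same identity holds for post-partum retention, with weight at three months in place of D.

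**3. Illustration of the precision lost.** Let f be the variance of gain before randomisation divided by the variance of gain after it, and ρ their correlation. Both are assumptions. With 213 and 426 women, two-sided 5% and 80% power, the detectable difference in gain after randomisation is

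(1.960 + 0.842) × √(1/213 + 1/426) = 0.235 SD of that gain.

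For the same effect in kilograms, the variance of unadjusted total gain is larger or smaller by the factor 1 + f + 2ρ√f. Power on unadjusted total gain is then:

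| f | ρ = −0.3 | ρ = 0 | ρ = +0.3 |
|---|---|---|---|
| 0.15 | 83% | 74% | 66% |
| 0.25 | 82% | 71% | 61% |
| 0.50 | 77% | 63% | 52% |
| 1.00 | 66% | 51% | 41% |

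Power usually falls below 80%, but it rises slightly when ρ is negative and f is small.

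Adjusting for the early gain leaves residual variance (1 − ρ²) relative to gain after randomisation. Since 1 + f + 2ρ√f = (√f + ρ)² + (1 − ρ²), this is never larger than the variance of unadjusted total gain. At ρ = −0.3 or +0.3 the factor is 0.91, the SD ratio is √0.91 = 0.954, and power is Φ(2.802/0.954 − 1.960) = Φ(0.977), about 84%. At ρ = 0 it is 80%. So even in the table's most favourable cell for the unadjusted analysis (83%), adjustment loses nothing.

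**4. Effect through length of gestation.** The planning figures are 16% preterm birth and a 30% reduction (Sample size calculation), a difference of 0.16 × 0.30 = 0.048. If a preterm delivery forgoes about 2 kg of gain (assumed), the mean shift is 0.048 × 2 = 0.096 kg, about 0.1 kg. Halving or doubling the 2 kg gives 0.05 or 0.19 kg.

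**5. Timing of the 16-week visit.** 16 + 16 = 32 to 20 + 16 = 36 weeks of gestation. It coincides with the end of the programme and precedes most deliveries.

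**The case against.** The strongest reply is that nothing here is an error. Whole-pregnancy gain is a clear and legitimate outcome, and early gain is balanced in expectation under intention-to-treat. Covariates are also commonly left to a statistical analysis plan, which was not at hand. The first two statements stand, so this is a weak analysis choice and not a contradiction. The third stands in part. The linear regression already planned can hold the covariates, which is why the remedy is so small. But the Protocol presents adjustment only as control of confounding, and the reason here is precision.

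Stronger readings are tempting, and the documents do not support them:

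- **That the comparison is biased.** It is not. Gain before allocation does not depend on arm.
- **That the loss equals a fixed factor of sample size.** A reader might assume that early gain carries 25% to 45% of the variance and infer 1/(1 − 0.25) = 1.3 to 1/(1 − 0.45) = 1.8 times as many women. No variance is given, a share of weeks is not a share of variance, and the sum presumes no correlation between early and later gain.
- **That total gain should be replaced by weight at the 16-week visit.** That changes the question from gain over pregnancy to gain during the programme. It omits the last weeks before delivery and makes missing values depend on early delivery, which is tied to a primary outcome.
- **That dependence on length of gestation is a serious distortion.** At about 0.1 kg it is mainly a point of interpretation.

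**Conclusion.** The point holds as a modest, no-cost improvement in precision. As defined, gestational weight gain includes everything gained before randomisation, 40% to 50% of a 40-week gestation by time, and the stated analysis does nothing to remove it. The consequence is usually a wider confidence interval and not a shifted estimate. How much wider cannot be stated, because the documents give no standard deviation; the power table is an illustration under assumed f and ρ.

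The conclusion assumes that weight is part of the anthropometry, that the baseline weight is taken before the first exercise session, and that exercise acts only after randomisation. It does not depend on any assumption about how accurate pre-gestational weight is.

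**What to change.** - Keep total gain as the defined secondary outcome. In the planned linear regression, adjust the arm comparison for weight at the baseline visit, pre-gestational weight and gestational age at baseline.
- Analyse post-partum weight retention with the same covariates.
- Do not adjust either comparison for gestational age at delivery. It is a post-randomisation variable tied to preterm birth, and conditioning on it could remove part of the effect or introduce bias. Note the small shift through duration when interpreting the result.
- Add a supporting analysis: a mixed model of measured weight at 8 and 16 weeks, adjusted for baseline weight. It does not rely on pre-gestational weight and is less tied to length of gestation. State its limits: it omits the last weeks before delivery, and women who deliver before the 16-week visit contribute only their 8-week weight.
- Confirm in one line that weight is measured at the baseline, 8-week and 16-week visits in both groups, and that the baseline value precedes exercise.

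The cost is a few sentences of analysis wording. If weight is measured as expected, no new visit or measurement is needed. The change should be fixed before any comparison by arm is made.
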